## Abstract

**Introduction:**

The aging of the population is a global phenomenon, with projections indicating a significant increase in the proportion of individuals aged 65 years and older by 2050. This demographic shift requires adapting emergency department (ED) services to meet the specific demands of older patients, who often present with multiple comorbidities and face challenges such as sensory and cognitive difficulties. EDs, traditionally designed for acute illness and injury management, may not be adequately equipped to meet the unique needs of this vulnerable population. This can result in suboptimal patient experiences, prolonged ED stays, increased hospitalizations, and poorer outcomes.

**Methods:**

This study protocol outlines a before-and-after study to evaluate the impact of implementing a comfort menu and cart on the experience and outcomes of older patients treated in the ED. The study will be conducted in the ED of Hospital Sírio-Libanês (HSL), a tertiary private hospital in São Paulo, Brazil. Patients aged 65 and older who presented to the ED will be eligible for inclusion. Participants will be recruited in two phases: pre-intervention and post-implementation of the comfort menu and cart. Data will be collected through patient and staff interviews, chart reviews, and a 30-day follow-up interview. Patient experience, staff experience, length of hospital stays, hospital costs, ED readmissions, falls, delirium incidence, quality of life, functional status, cognitive performance, and mortality will be assessed.

**Expected results:**

We expect to demonstrate the positive impact of implementing the comfort menu and cart in the ED on patient-centered outcomes. We anticipate improvements in the experience of older patients and medical and multidisciplinary staff, and hope to identify improvements in other exploratory outcomes.

**Trial registration number:**

ClinicalTrials.gov NCT06681376.

## Introduction

The aging of the population is a global phenomenon, with projections indicating a significant increase in the proportion of individuals aged 65 years and older by 2050 [1]. This demographic shift requires adapting emergency department (ED) services to meet the specific demands of older patients, who often present with multiple comorbidities and face challenges such as sensory and cognitive difficulties [2,3]. EDs, traditionally designed for acute care, may not adequately address the complex needs of this population, leading to suboptimal patient experiences and potentially poorer outcomes.

International organizations have recognized the need for specialized geriatric ED care and have published guidelines to improve the quality and safety of care for older adults in this setting [4,5]. The American College of Emergency Physicians, in collaboration with the American Geriatrics Society, the Emergency Nurses Association, and the Society for Academic Emergency Medicine, published the “Geriatric Emergency Department Guidelines” in 2014 [4]. They provide comprehensive recommendations on modifying the physical environment, training staff, and implementing specific care processes for older patients [4]. Similarly, the European Task Force on Geriatric Emergency Medicine published recommendations in 2020 emphasizing the importance of comprehensive assessment, including screening for delirium, depression, and fall risk [5].

Despite these guidelines, the implementation of evidence-based geriatric ED care practices remains inconsistent, and research exploring innovative interventions to improve the older patient experience is still in its early stages. A recent study by Lichen et al. (2021) demonstrated the positive impact of non-pharmacological interventions, specifically a “comfort cart,” on the experience of older patients in the ED [3]. This study highlighted the potential of relatively simple, low-cost, patient-centered interventions, such as extra blankets or pillows, a personal hygiene kit, items for distraction, and items to enhance communication like reading glasses and hearing amplifiers, to enhance the comfort, well-being, and ability to communicate of older adults during their ED stay. Similar initiatives, such as the comfort care cart described by Stolzman et al. (2020) in the intensive care unit, have also shown promising results in improving patient and family experience [6]. These studies suggest a growing recognition of the importance of addressing the holistic needs of older patients in acute care settings, beyond solely focusing on medical treatment.

Our study aims to build upon this emerging body of literature by implementing and evaluating the impact of a comfort menu and cart in the ED of a tertiary philanthropic hospital in Brazil. This will be the first study to explore this intervention in older adults in the ED setting since its original description by Lichen et al. [3], and it will be the first to generate evidence on its impact on patient-centered outcomes measured up to 30 days after the initial ED visit. By comprehensively assessing the impact of this intervention on patient experience, staff experience, and clinical outcomes, our study will generate valuable evidence to inform the development and implementation of this innovative non-pharmacological strategy to improve the care of older adults in EDs.

### Objectives

#### Primary objective.

Evaluate the impact of implementing a comfort menu and cart on the experience of older patients treated in the ED.

#### Secondary objectives.

Evaluate the impact of implementing a comfort menu and cart on the experience of medical and multidisciplinary staff involved in caring for older patients treated in the ED.Evaluate the impact of implementing a comfort menu and cart on other exploratory outcomes, such as length of hospital stay, hospital costs, and patient-centered outcomes up to 30 days in older adults treated in the ED, including readmissions, falls, delirium incidence, quality of life, functionality, and cognitive performance.

## Methods

### Study design

This study will utilize a quasi-experimental, before-and-after design [7]. Schedule of enrolment, assessments and intervention is summarized in Fig 1.

**Fig 1 pone.0332773.g001:**
[figure not shown]
Schedule of enrolment, interventions, and assessments (SPIRIT).

### Study population

#### Inclusion criteria.

ED attendance at Hospital Sírio-Libanês (HSL), São Paulo, Brazil.Age ≥ 65 years.Capacity to consent and respond to the interview or the presence of a companion capable of doing so.

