#### Exclusion criteria.

Decline to participate in the study or use the comfort menu and cart.Absence of a companion able to consent to study participation and provide necessary information for patients with altered mental status or cognitive impairment.Decreased level of consciousness.Hemodynamic instability.Acute respiratory failure.Inability to be contacted by phone for the follow-up interview.

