**Table pone.0332773.t001:** 

Questions adapted from Lichen et al. (2021)			
* Question *		* Response options *	
*During your stay in the ED, what was your average comfort level?*		Very comfortable; Comfortable; Somewhat comfortable; Somewhat uncomfortable; Uncomfortable; Very uncomfortable	
*As a person in the emergency department, do you feel you were offered care specific to your individual needs (I.e. needs related to communication, hearing, vision, etc.)?*		Strongly agree; Somewhat agree; Neither agree nor disagree; Somewhat disagree; Strongly disagree	
Additional questions in the post-implementation phase			
*Did you use any of the items or services offered in the Geriatric Cart?*		Yes; No	
*Knowing that these items or services were available, even if I did not use them, made me feel more comfortable*		Strongly agree; Somewhat agree; Neither agree nor disagree; Somewhat disagree; Strongly disagree	
*The items I requested from the comfort cart made me feel more comfortable during my visit today*		Strongly agree; Somewhat agree; Neither agree nor disagree; Somewhat disagree; Strongly disagree	
*Having the comfort cart available improved my overall experience today*		Strongly agree; Somewhat agree; Neither agree nor disagree; Somewhat disagree; Strongly disagree	
*Having the comfort cart gave me more independence during my visit today*		Strongly agree; Somewhat agree; Neither agree nor disagree; Somewhat disagree; Strongly disagree	

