**Table pone.0332773.t002:** 

Demographics	Full name, medical record number, ED visit number, date of birth, postal code, sex, date and time of ED admission
**Source of information**	If not the patient, the source’s full name, date of birth, sex, and relationship to the patient will be recorded
**Sensory deficits**	Presence and type of visual and/or hearing impairments
**History of falls**	Number of falls in the past year, circumstances surrounding the falls
**Comorbidity**	Assessed using the Charlson Comorbidity Index (CCI) [12–15]
**Risk of falls**	Assessed using the Memorial Emergency Department Fall Risk Assessment Tool (MEDFRAT) and the Carpenter instrument [16,17]
**Frailty**	Assessed using the Clinical Frailty Scale (CFS) version 2.0 [18,19]
**Clinical severity**	Assessed using the National Early Warning Score (NEWS) 2 [20,21]
**Mood**	Assessed using the 15-item Geriatric Depression Scale (GDS-15) [22]
**Geriatric vulnerability**	Assessed using the PRO-AGE Score [10]
**Acute mental status change (delirium)**	Assessed using the Delirium Triage Screen (DTS) and Brief Confusion Assessment Method (bCAM) [23]
**Quality of life**	Assessed using the Euro Quality of Life Instrument – 5D (EQ-5D) [24]
**Functionality**	Assessed using the Katz Index, Barthel Index, and Lawton Scale [25–27]
**Cognitive performance**	Assessed using the 10-Point Cognitive Screener (10-CS) [28]

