**Table pone.0332773.t004:** 

ED readmissions	Number of ED visits since the initial visit
**Falls**	Number of falls since the initial visit
**Delirium incidence**	Assessed using the Family Confusion Assessment Method (FAM-CAM) [29] administered to a family member or caregiver
**Mood**	Assessed using the GDS-15
**Quality of life**	Assessed using the EQ-5D
**Functionality**	Assessed using the Katz Index, Barthel Index, and Lawton Scale
**Cognitive performance**	Assessed using the 10-CS
**Mortality**	If the patient has passed away, the date and cause of death will be recorded

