### Intervention

The comfort menu and cart will be implemented after the pre-intervention data collection phase is completed. The menu will list the items available on the cart and will be presented to eligible patients in printed or digital format (on a tablet). The cart will be placed in an easily accessible area within the ED. Approximated retail prices have been previously reported [3].

A one-month dedicated rollout period will precede the commencement of post-intervention participant enrollment. This phase is designed for comprehensive staff training on the proper use and components of the comfort menu and cart, including familiarization with all available items and menu options. Additionally, this period will ensure all necessary equipment is adequately prepared and any potential logistical challenges associated with the cart’s implementation are identified and resolved, thereby optimizing the fidelity and effectiveness of the intervention before data collection for the post-intervention group begins.

Comfort Cart Contents:

Hot and cold packs;Extra blanket and pillow;Face towel;Gloves and hat;Personal hygiene kit (toothbrush, toothpaste, cotton swabs, sleep mask, comb, deodorant, hand lotion);Items for distraction (magazines, word search puzzles, playing cards, coloring pages);Items to enhance communication (reading glasses, magnifying glass, penlight, cell phone charger, notepad, sound amplification device).

Comfort Menu Options:

Physiotherapy assessment;Conversation with chaplain, concierge, or social worker;List of resources for older adults needing community services;Home care assistance.

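### Companions may answer the subjective primary items in the patient's place, respondent type is recorded but not among the named adjustment variables, and no rule reserves GDS-15 or 10-CS for the patient

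*Protocol article*

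**What the plan says.** Under Inclusion criteria, eligibility rests on "Capacity to consent and respond to the interview or the presence of a companion capable of doing so". Exclusion criteria show when a companion is indispensable, by excluding "Absence of a companion able to consent to study participation and provide necessary information for patients with altered mental status or cognitive impairment". Neither section says which items a companion may answer.

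The primary objective is assessed with the two adapted questionnaires in the Initial interview section. The first item is "During your stay in the ED, what was your average comfort level", with six ordered answers. The second questionnaire has eight items, and on all of them an answer of not knowing is classed as a problem.

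The data table in the same section states, for source of information: "If not the patient, the source’s full name, date of birth, sex, and relationship to the patient will be recorded". It also lists GDS-15 for mood and 10-CS for cognitive performance. The Follow-up interview table repeats both by telephone at 30 days (for mood, "Assessed using the GDS-15"), together with EQ-5D, Katz, Barthel and Lawton. Only the family delirium instrument, FAM-CAM, has a named respondent there.

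Data management and statistical analysis says that analyses will be adjusted for confounders and gives baseline frailty, cognitive impairment and clinical severity as examples. Respondent type is not among them.

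**The concern.** A companion's answer to the comfort item is an estimate of someone else's internal state. The protocol treats a third-party comfort rating as a separate measurement when staff give it: staff have their own wording, analysed under a secondary objective. Companions have no such version, so nothing in the text stops their rating from standing as the patient's own. The limitations paragraph in the Discussion mentions self-reported data from patients and staff, but not companions.

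The primary comparison is between two calendar periods, and no randomisation balances who answers. If companions score systematically differently from patients and their share differs between periods, that difference enters the estimated effect of the cart.

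The second problem is validity. GDS-15 asks about the patient's mood, and 10-CS is described as a measure of cognitive performance. A companion can only guess the first and cannot perform the second. Such values cannot be repaired in the analysis. For the other scales repeated at 30 days, an unrecorded change of respondent could look like a change in quality of life or function.

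**Working it through.** **The plan's own figure.** Sample size calculation gives a difference of 0.98 on a 1-to-6 scale, 90% power, 5% significance and 132 per group. No SD is stated, so 132 can be neither reproduced nor refuted. Solving back for a two-sided test:

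SD = 0.98 × √(132/2) / (1.960 + 1.282) = 2.456.

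That is close to 2.5, about the largest SD possible on such a scale, so I also use an assumed SD of 1.2.

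**Bias from respondent mix.** If the true effect is zero and companions differ from patients by a constant gap:

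bias = (change in companion share) × (companion-patient gap).

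With a share falling from 35% to 20% and a gap of 0.5 to 1.0 point (both assumed):

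- 0.15 × 0.5 = 0.075 points; 0.075/0.98 = 8%.
- 0.15 × 1.0 = 0.15 points; 0.15/0.98 = 15%.

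**Effect on the false-positive rate.** This is P(|Z + bias/SE| > 1.96), with SE = SD × √(2/132), for an unadjusted comparison of means. At SD 1.2, SE = 0.148 and the smallest significant difference is 0.29. At SD 2.456 it is 0.593.

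| Shift in share | Gap | Bias | % of 0.98 | False positive, SD 1.2 | False positive, SD 2.456 |
|---|---|---|---|---|---|
| 10 points | 0.5 | 0.05 | 5.1 | 6.3% | 5.3% |
| 20 points | 0.5 | 0.10 | 10.2 | 10.4% | 6.3% |
| 20 points | 1.0 | 0.20 | 20.4 | 27.3% | 10.1% |
| 30 points | 1.0 | 0.30 | 30.6 | 52.8% | 16.8% |

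At the low end, a 5-point shift with a gap of 0.25 gives 0.0125 points, or 1.3% of 0.98.

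**Problem items.** If 20% of companions and 5% of patients answer that they do not know (assumed), the same fall in share moves an item by (0.35 − 0.20) × (0.20 − 0.05) = 2.25 percentage points.

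**GDS-15 and 10-CS.** At a companion share of 20% to 35% (assumed), 132 × 0.20 = 26 to 132 × 0.35 = 46 patients per phase could lack a valid value. This is an upper figure, because it supposes that no patient with a companion as source could be tested.

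**Cost of a self-responder analysis.** With companion shares of 10, 20, 30 and 40% (assumed), 119, 106, 92 and 79 patients per group remain. Power for 0.98 is then 87, 83, 77 and 71% at SD 2.456, and at least 98% at SD 1.5 or less.

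**The case against.** The strongest reply is that nothing in the article says patient and companion answers will be analysed as one. The source is recorded, the covariate list is open, and a statistical analysis plan that is not shown could use the variable. That stands: pooling is inferred from silence and is not a stated intention. It does not remove the point, because who may answer an item is settled by eligibility and data collection, which this document does fix.

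Exclusion criteria tie the need for a companion to mental status or cognition, and cognitive impairment is already a named covariate. That covers part of the route. It does not cover all of it, since the inclusion criterion does not confine companion answers to impaired patients.

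A reader might infer a stronger claim: that the cart's own aids ("Items to enhance communication (reading glasses, magnifying glass, penlight, cell phone charger, notepad, sound amplification device") let more patients answer for themselves in the second phase, and so shift the mood and cognition results. The documents do not support this. They do not link companion use to hearing or vision loss. The 30-day mood and cognition measures are taken by telephone, and no section says the aids are available then. A 10-CS that a companion cannot take becomes missing or invalid; it does not shift.

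The direction for the problem items is also uncertain. Two of them concern the family member, where a companion may know more than the patient, and some others count information given to family as no problem.

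**Conclusion.** The point holds in limited form. As written, the primary outcome can mix self and companion ratings, and the named adjustment variables do not separate them. A difference in companion share between phases could therefore be taken in part for an effect of the cart. Companion share, companion-patient gap and SD are all absent from the documents, so every size above is illustrative. Moderate assumed values give a bias that is small against 0.98. Only large shifts with a large gap raise the false-positive rate substantially. The missing respondent rule for GDS-15 and 10-CS is a separate gap in validity, and it does not depend on those assumptions. The point does not overturn the design, but it should be settled before recruitment.

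**What to change.** - Decide who responds at enrolment, before the menu is offered, by the same rule in both phases. Adjustment alone would not suffice if the intervention itself influenced who answers.
- Add respondent type to the adjustment set for the experience outcomes, and report it by phase.
- Prespecify a sensitivity analysis of the primary comparison restricted to patients who answered for themselves.
- Accept GDS-15 and 10-CS only when the patient answers, at either time point; otherwise record 'not assessable'.
- For the other scales repeated at 30 days, record the respondent again and account for any change. Do not lock in the respondent chosen at consent: a patient who could not answer in the ED may be able to at 30 days.

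The cost is one protocol paragraph and one REDCap branch. The source is already collected at the initial interview; recording it at 30 days adds one field. The timetable runs REDCap development to March 2026 and starts recruitment in April 2026, so the change fits before the first patient. The downside is somewhat fewer usable GDS-15 and 10-CS values, neither of which serves the primary objective.

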#### Exclusion criteria.

Decline to participate in the study or use the comfort menu and cart.Absence of a companion able to consent to study participation and provide necessary information for patients with altered mental status or cognitive impairment.Decreased level of consciousness.Hemodynamic instability.Acute respiratory failure.Inability to be contacted by phone for the follow-up interview.

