### Data management and statistical analysis

All study data will be collected and managed using Research Electronic Data Capture (REDCap) [30], a secure web-based application. Research assistants will use tablets with online access to the REDCap database for direct data entry and informed consent procedures.

For the primary objective evaluating the impact of the comfort menu and cart on the experience of older patients we will use the questionnaire adapted from Lichen et al. (2021) and McCusker et al. (2018). For the secondary objectives evaluating the impact of a comfort menu and cart on the experience of medical and multidisciplinary staff involved in caring for older patients treated in the ED, we will use the the questionnaire adapted from Lichen et al. (2021).

Data analysis will be performed using Stata version 17 (StataCorp, College Station, TX). All statistical tests will be two-tailed with an alpha error of 0.05. Numerical variables will be reported as means and standard deviations or medians and interquartile ranges (IQR) depending on their distribution, which will be assessed visually and using the D’Agostino-Pearson test for normality. Categorical variables will be described as absolute counts and proportions. Numerical variables will be compared using Student’s t-test or ANOVA for normal distributions and Wilcoxon or Kruskal-Wallis tests for non-normal distributions. As appropriate, categorical variables will be compared using the chi-square test or Fisher’s exact test. Analyses will be adjusted to account for potential confounding variables, such as baseline frailty, cognitive impairment, and clinical severity. Missing data will be handled though mixed effects model.

All relevant data from this study will be made available upon study completion.

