### Ethics and dissemination

Ethical approval for this study has been granted by the Institutional Review Board of HSL (*Comitê de Ética em Pesquisa do Hospital Sírio Libanês/ Sociedade Beneficente de Senhoras*): certificate n^o^ 85870125.4.0000.5461, decision n^o^ 7.436.261, dated March 12 2025. All participants, or their legal representatives for those with cognitive impairment, will provide written informed consent before any study procedures are initiated.

Given that the study employs a quasi-experimental design, with no alteration to the participants’ clinical procedures, and includes participants both before and after the intervention, the informed consent form will not disclose details of the intervention in order to mitigate information bias. The purpose is to ensure that participants are unaware of the intervention studied, thereby preventing their perception of care from being affected by a perceived comfort, either absent or present, depending on their study phase.

The results will be shared with the academic community through peer-reviewed publications and presentations at relevant conferences to inform future clinical practice and research.

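### Excluding patients who decline to use the cart can act only in the post-intervention phase, so the two groups are selected by different rules; the direction and size of the resulting bias are unknown

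*Protocol article*

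**What the plan says.** All places are in the protocol article.

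- **Exclusion criteria:** one list for the whole study includes "Decline to participate in the study or use the comfort menu and cart".
- **Study design:** "This study will utilize a quasi-experimental, before-and-after design".
- **Intervention:** "The comfort menu and cart will be implemented after the pre-intervention data collection phase is completed". The menu is then shown to eligible patients on paper or on a tablet.
- **Ethics and dissemination:** "the informed consent form will not disclose details of the intervention in order to mitigate information bias". The stated aim is that participants do not know which intervention is studied.
- **Primary objective:** "Evaluate the impact of implementing a comfort menu and cart on the experience of older patients treated in the ED".
- **Initial interview, additional post-implementation questions:** "Did you use any of the items or services offered in the Geriatric Cart", answered Yes or No, and an agreement item, "Knowing that these items or services were available, even if I did not use them, made me feel more comfortable".
- **Data management and statistical analysis:** "Analyses will be adjusted to account for potential confounding variables, such as baseline frailty, cognitive impairment, and clinical severity".

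**The concern.** In a before-and-after study the two groups are comparable only if the same kinds of patient enter both. One of these exclusions has no counterpart in the first phase. A post-phase patient who refuses the cart is removed, while a patient of the same kind in the pre-phase stays in, because there was nothing to refuse.

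Refusal is unlikely to be unrelated to the outcome. A patient who is already comfortable may decline for lack of need, and a very ill or low patient may decline everything. Either pattern shifts the mean comfort of the post group for reasons unrelated to what the cart does.

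The rule also narrows the question. Implementing a cart in an emergency department includes offering it to people who do not want it, and the primary objective is worded for older patients treated there in general.

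**Working it through.** **1. When the rule can act.** The cart is introduced after the pre-phase closes, and the consent form keeps its details back, so a pre-phase patient cannot decline it even hypothetically. The timetable places rollout in June 2026, the last pre-phase month, but the article describes rollout as training and preparation, and implementation is listed from July. The criterion can therefore remove patients in the post phase only.

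**2. Whom it removes.** The Yes/No use item and the item worded for non-users show that some enrolled post-phase patients are expected to have used nothing. The criterion thus removes those who decline, not all those who do not use. No text tells the research assistant how to separate the two, so the same patient could be classified either way.

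**3. Form of the bias.** Let q be the share of otherwise eligible patients who refuse or would refuse. Let A and R be the mean comfort, without any cart effect, of non-refusers and refusers.

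- Pre-group mean: (1 − q)A + qR
- Post-group mean, refusers excluded and cart inert: A
- Difference: A − (1 − q)A − qR = q(A − R)

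The sign is that of A − R, on which the documents give no information.

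**4. Inputs for size.** From the article: 132 per group, two-sided 5% level, 90% power, planned difference 0.98 on a 1–6 scale. Not given: q, A − R and the SD. The sample size states no SD or dropout allowance, so 132 can be back-solved but not reproduced. Without a dropout allowance,

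SD = 0.98 × √(132/2) / (1.960 + 1.282) = 2.456,

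which is close to 2.5, the largest SD possible on a 1–6 scale. It serves here as the upper end of a range; 1.25 and 1.5 are assumed lower values.

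**5. Illustration.** Assumed shifts, as q × gap: 0.20 × 0.5 = 0.10; 0.30 × 0.5 = 0.15; 0.40 × 0.5 = 0.20; 0.30 × 1.0 = 0.30. These are 10%, 15%, 20% and 31% of 0.98. The standard error is SD × √(2/132): 0.154 at SD 1.25, 0.185 at SD 1.5 and 0.303 at SD 2.46. Rejection rates of a two-sided t-test when the cart does nothing:

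| Shift (either sign) | SD 1.25 | SD 1.5 | SD 2.46 |
|---|---|---|---|
| 0.10 | 9.9% | 8.4% | 6.3% |
| 0.15 | 16.3% | 12.8% | 7.8% |
| 0.20 | 25.4% | 19.0% | 10.1% |
| 0.30 | 49.3% | 36.7% | 16.7% |

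If few patients decline the shift is smaller: 0.10 × 0.5 = 0.05 gives 5.8% at SD 1.5 and 5.3% at SD 2.46 (normal approximation).

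**6. Effect of keeping refusers.** If the effect is 0.98 in non-refusers and zero in refusers, the effect in everyone offered the cart is 0.98 × (1 − q): 0.88, 0.78 and 0.69 for q of 10%, 20% and 30%. Power with 132 per group (normal approximation) is then 83%, 74% and 62% at SD 2.456, and 99.8%, 98.9% and 96.0% at SD 1.5.

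**The case against.** Four counter-arguments deserve an answer.

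- **Non-users stay in.** A reader might infer that the post group holds only users and that the study has become one of users. The questionnaire contradicts this, since it provides for enrolled patients who used nothing. This objection stands: only outright refusers are lost.
- **Concealment may disarm the rule.** If the intervention is hidden at consent, refusal cannot easily act at enrolment, and no text describes removing a consented patient later. This stands in part. The consent form withholds details, but the menu is shown to eligible patients, so refusal can occur at that point. Whether and when the criterion is then applied is left open, and so a bias is possible but not demonstrated.
- **The sign is unknown.** It is tempting to read the rule as inflating the cart's benefit. Nothing in the article supports that. If refusers are mainly patients who are already comfortable, excluding them works against the cart and could mask a benefit.
- **Adjustment helps.** Frailty, severity (NEWS2), comorbidity, mood (GDS-15) and cognition are all collected at the initial assessment, and the analysis adjusts for confounders of this kind. So it would be too strong to say that nothing can be done in the analysis. But willingness to use the cart is not observed in the pre group, so would-be refusers there cannot be identified, and mitigation is partial.

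**Conclusion.** The point holds in this form: as written, the criterion can exclude patients in the post phase only. It therefore sets different selection rules for the two groups, drops outright refusers from an estimate aimed at implementation, and conflicts with a questionnaire that expects non-users. These conclusions follow from the text and need no assumed figure.

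The amount of bias is not established. Its direction is unknown, and the false-positive rates of about 6% to 49% rest wholly on assumed decline rates, gaps and SDs. A reader might take the 49% as the expected error rate. It is one corner of the range, needing 30% refusal, a full-point gap and SD 1.25 together. If refusal is rare the effect is small, but the article sets no limit on it.

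The criterion should be corrected before recruitment opens, planned for April 2026, because no outcome data will be collected on refusers who are excluded and the loss could not be made good afterwards.

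**What to change.** Delete the last seven words of the criterion, from the word 'or' onwards, so that it covers refusal of study participation only and eligibility is the same in both phases. Add one sentence on the analysis population: every eligible consenting patient in the post phase is analysed in the post group, whether items were used, not used or refused. Report uptake from the existing Yes/No item, and show results in users only as a descriptive secondary analysis.

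The cost is a small wording change, made before the first patient is recruited, and no new data item. The downside is that the estimated effect, and with it the power, may be lower if refusers gain nothing: slightly at SD 1.5, more clearly if the SD is near 2.46. That lower effect is nonetheless the one the primary objective asks about.
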